##### CPR Evaluation

We will evaluate the CPRs on the test set ***t*** using discrimination, calibration, and clinical utility. The same methodology previously applied to CHA_2_DS_2_-VASc will be used to assess the discrimination and calibration of the newly developed CPRs. See Section 2.12.4. Clinical utility will be measured using net benefit (NB) via decision curve analysis (DCA). Although a CPR with better discrimination and calibration should, in theory, better guide clinical management, discrimination and calibration cannot determine whether a CPR aids decision making or which of several CPRs leads to better decisions. This is especially true when some CPRs have better discrimination and others better calibration. The shortcomings of conventional measures of performance are due to the fact that they do not incorporate information on consequences. DCA incorporates consequences by considering the tradeoffs between the benefits of true positives and the harms of false positives across a range of risk thresholds that reflect a spectrum of possible patient and clinician preferences [100]. It achieves this by calculating the NB for each risk threshold (*p**t*), which is defined as the number of true positives corrected for the number of false positives weighted by the odds of the risk threshold, all divided by the sample size (*N*) [124]. This is equivalent to the proportion of true positives in the absence of false positives (i.e., perfect specificity). To effectively use CPRs in clinical management, it is necessary to specify the risk thresholds at which intervention would be warranted. For early secondary prevention of AFAIS, oral anticoagulation is the treatment, and risk thresholds within 0.01—0.20 are reasonable. We will thus calculate the true positives and false positives for each CPR across the 0.01–0.20 risk threshold range and compute NB using the following formula:$$NB=\frac{\;\mathrm{True}\;\mathrm{positives}\;}{N}-\frac{\;\mathrm{False}\;\mathrm{positives}\;}{N}\left(\frac{p_{t}}{1-p_{t}}\right).\;$$

NB will be plotted on the *y*-axis against risk threshold on the *x*-axis to yield a decision curve for each CPR. These curves, including the one for CHA_2_DS_2_-VASc, will be presented in a single figure to facilitate comparison. Additionally, we will plot lines representing the default strategies of ‘treat all’ and ‘treat none’, corresponding to scenarios where all or no patients are assumed to suffer 90-day recurrence, respectively. Incidentally, these lines will intersect at the observed prevalence of 90-day recurrence in our test set. A CPR will be considered clinically useful at a given risk threshold only if its NB exceeds that of both default strategies. Conversely, if a CPR’s NB is lower than either default strategy, it will be deemed clinically harmful. Our initial analysis will focus on determining whether the CPRs have higher NBs than the default strategies across the selected risk thresholds. We will then proceed to comparing the CPRs, ranking them based on descending NB, and identifying the three CPRs with the highest clinical utility (Table 3 and Table 4).

If an augmented CPR ranks among the three highest, we will perform test tradeoff analysis to compare it with the closest-ranking non-augmented CPR. The test tradeoff, calculated as Δ*NB*, represents the minimum number of additional tests per true positive required to justify the augmented CPR’s use, considering its added cost [124]. Of course, in our case, cost is not financial, but the additional time and reduced convenience associated with augmented CPRs, which include accompanying rules and are thereby more unwieldy than their non-augmented counterparts. If the NB differences across thresholds are small, the test tradeoff will be large, suggesting that the simpler CPR may be better, all things considered. After all, CHA_2_DS_2_-VASc owes its widespread adoption to its parsimonious, back-of-the-envelope nature. For clarity, we will report test tradeoffs in terms of both true positives and true negatives. The same approach will be applied to CPRs developed using MLP, where the test tradeoff will help decide whether the increased NB justifies the involvement of a less interpretable model. Ultimately, the purpose of reporting test tradeoffs will be to highlight which CPRs—if any—would be conveniently deployable without sacrificing significant clinical utility, and *not* to dismiss higher cost CPRs from future consideration.

Finally, we will also report the clinical utility of the LR- and XGBoost-powered CPRs and CHA_2_DS_2_-VASc on the non-AF cohort. The purpose of this is to establish whether they remain better than the default strategies when exposed to a large set of patients that non-randomly differs from the training dataset.

Table 3 and Table 4 should appear after Section “CPR Evaluation”.

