
## 1. Introduction

Atrial fibrillation (AF) is the most common cardiac arrhythmia [1] and confers a fivefold greater risk of acute ischaemic stroke (AIS) relative to normal sinus rhythm [2]. AF-related AIS (AFAIS) is reported to account for 13–26% of global AIS burden [3], and its association with greater infarction size, severity, disability, mortality, and cost compared to AIS of non-thromboembolic pathogenesis is well-documented [4,5,6,7,8]. Fortunately, AFAIS is known to be highly preventable with oral anticoagulants (OACs) [9]. Current guidelines recommend OACs for primary and secondary prevention on the basis of CHA_2_DS_2_-VASc [10,11], a prognostic clinical prediction rule (CPR) that estimates annual risk of AFAIS. However, it has been reported that only 32% of AFAIS survivors are prescribed OACs for secondary prevention in a guideline-adherent manner [12,13]. In fact, several studies have shown that patients with higher CHA_2_DS_2_-VASc scores were paradoxically less likely to receive antithrombotic therapy [1,14,15]. While this ‘anticoagulation paradox’ is partly attributable to the fact that a high CHA_2_DS_2_-VASc score implies high bleeding risk [16], there is also concern that OACs are being omitted for non-therapeutic reasons despite RCT evidence substantiating that recurrence rates are highly modifiable with OACs [17]. This is alarming given that 1-year recurrence rates have been reported to be as high as 30% [18,19]. We contend that the absence of research ascertaining the predictive performance and clinical utility of CHA_2_DS_2_-VASc with regard to recurrence is partly to blame. Indeed, it is a major limitation that patients with and without stroke history were not routinely differentiated in studies validating CHA_2_DS_2_-VASc [20]. Rather, validation studies employed numerical scores to divide subjects into risk strata irrespective of whether a score of 4 belonged to a 75-year-old female patient with diabetes or a 60-year-old male with history of hypertension, stroke, and myocardial infarction, for example. Therefore, data on the performance of CHA_2_DS_2_-VASc among cohorts with previous AIS is scarce, and existing studies have reported poor discrimination, with C-statistics generally below 0.6 [21]. This prompted us to design an external validation study for CHA_2_DS_2_-VASc in AF patients scoring ≥ 2 points after having suffered an AIS.

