### 2.3. Study Population

The filters applied in screening the repository were that the patient (1) had an AF diagnosis, and (2) was treated with vitamin K antagonists (VKAs) or without any antithrombotic medication. Criterion (2) was informed by the fact that contributing trials predated the introduction of novel oral anticoagulants (NOACs).

This yielded 2763 patients with documented age; sex; pre-stroke modified Rankin Scale (mRS) score; 90-day mRS; baseline National Institutes of Health Stroke Scale (NIHSS) score; 30- and 90-day NIHSS; medical history including congestive heart failure (CHF), hypertension, hyperlipidaemia, diabetes mellitus (DM), myocardial infarction (MI), coronary artery disease (CAD), transient ischaemic attack (TIA), prior AIS, and tobacco use; intravenous thrombolysis with recombinant tissue plasminogen activator (IVT); and onset-to-thrombolysis time (OTT). Medication administration records and adverse event records were also extracted: the former were screened for start and end days of VKA administration relative to AIS and the latter were screened for 7- and 90-day recurrence; 7- and 90-day haemorrhagic transformation (HT); and 90-day mortality.

Patients without an AF diagnosis were also retained under the condition that they were treated with vitamin K antagonists (VKAs) or without any antithrombotic medication. This yielded 7809 patients, whose records documented the same information as above.

The AF cohort will be used for primary and secondary analyses, while the non-AF cohort will serve exclusively for secondary analyses.

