### 2.4. Predictor Variables

The predictor variable in the validation analyses is CHA_2_DS_2_-VASc score, computed on the basis of its constituent features. It is computed as follows: 1 point for each of CHF, hypertension, DM, vascular disease (MI, CAD, or peripheral artery disease), age 65–74 years, and sex category (female), and 2 points for each of age ≥ 75 years and antecedents of AIS or TIA [24]. All features were measured at baseline, and, with the exception of age, all were binary encoded. As one of the more subjective items considered by CHA_2_DS_2_-VASc, peripheral artery disease was seldom recorded by contributing trials. Hence, MI and CAD will underlie the vascular disease feature.

The predictor variables in the updating analyses are the constituent features of CHA_2_DS_2_-VASc—omitting S_2_, which provides no discriminatory information in a cohort where all patients inherently have the same value (i.e., 2)—and previous stroke. Crucially, since secondary prevention is, by definition, aimed at patients having sustained an AIS, previous stroke is defined herein as any episode of AIS *prior* to the one that prompted recruitment. Besides preserving the familiar 7-feature structure of CHA_2_DS_2_-VASc, incorporating this variable in the updated CPR is very apropos in the modern-day context of effective treatment and demographic ageing which signify that many patients survive one or more strokes.

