### 2.5. Confounding Variables

The measured confounding variables are antithrombotic treatment (VKAs or none), start and end days of VKA administration, IVT, and OTT. Antithrombotic medication, IVT, and the timings of their administration constitute all information available about treatments received by participants.

Actions taken to blind the assessment of predictors or confounding variables in contributing trials, if any, were not recorded by VISTA. Qualifications and demographic characteristics of predictor assessors were not available.

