The sample sizes derived from steps 1, 2, 3, and 4 were 288, 344, 680, and 459 patients, respectively. We therefore deemed a minimum total sample size of 680 patients necessary for CPR development. Given that our sample size is 2763 patients and the fact that we will perform validation and updating (and not development from scratch), we contend that our regression analyses are adequately powered. Of note, 75% of our dataset (*n* = 2072 patients) will be used for regression model training and the remaining 25% (*n* = 691 patients) will be reserved for testing. The fact our test set alone exceeds the required 680 patients further supports our sample size.

ML and DL techniques are inherently more data-intensive than regression [85]. This is because the number of predictors they consider far exceeds that of regression, even when the same set of predictors is considered, because they examine multiple interaction terms [84]. Unfortunately, guidance for a priori sample size calculations is currently lacking for most ML/DL techniques [86]. However, if closely related data are readily available, it has been suggested that inspecting model learning curves in the related dataset can be valuable to estimate the required sample size for the main dataset [87,88]. We will therefore explore the observed power of our non-regression models by means of learning curves on our non-AF dataset, as well as via a key information theoretic metric: Kullback–Leibler (KL) divergence.

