### 2.11. VISTA vs. the CHA_2_DS_2_-VASc Development Dataset

The CHA_2_DS_2_-VASc development dataset was extracted from the Euro Heart Survey (EHS) on AF, a multi-centre prospective observational study whose methods have previously been described [91]. Patients were enrolled in EHS if they were 18 years or older and had an electrocardiogram or Holter recording showing AF during the qualifying admission/consultation or in the preceding 12 months. The development study [92] screened EHS for patients with (1) absence of mitral stenosis and previous heart valve surgery, and (2) use of neither VKAs nor heparin at discharge. This yielded 1577 patients documenting all of the variables we have access to, with the addition of PAD. Outcome variables were thromboembolism (defined as AIS, peripheral embolism, or pulmonary embolism) and all-cause mortality at 1-year follow-up. Accounting for patients lost to follow-up, the development dataset comprised 1150 patients with known survival status and 1084 with known thromboembolic status at 1 year.

Our dataset and EHS enrolled patients from hospitals and acute centres across 38 and 35 countries, respectively. Our centres were globally distributed while the Euro Heart Survey was pan-European. Recruitment ran from 1992 to 2006 for the VISTA contributing trials and September 2003 to July 2004 for EHS. The differences in the eligibility criteria of VISTA’s contributing trials and EHS reflect their stroke- and AF-centric aims, respectively. Our less-stringent screening filters were a deliberate attempt to enhance the applicability of CHA_2_DS_2_-VASc to a broad subset of AF patients, not least because of the already stringent inclusion and exclusion criteria of VISTA’s contributing trials relative to that of the observational studies comprising EHS. Finally, the differences in outcome variables reflect our focus on secondary prevention as opposed to primary prevention.

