##### Variable Encoding

Comorbid features, tobacco use, IVT, recurrence, and mortality will be encoded as: absent = 0 and present = 1. Sex will be encoded as: male = 0 and female = 1, as stipulated by CHA_2_DS_2_-VASc. The number of days of VKA use over 90-day follow-up will be treated as a continuous variable.

Age requires a more nuanced approach to preserve the structure of the existing CPR. For the validation analyses, age will be encoded as usual: age < 65 years = 0, 65–74 years = 1, and ≥75 = 2. For the updating analyses, the age categories (<65, 65–74, ≥75 years) will be one-hot encoded. This approach involves creating three binary variables and thereby avoids the introduction of an artificial ordinal scale that could imply a linear progression of risk across age groups. As such, it respects the non-linear risk increments that have been reported with advancing age and acknowledged by the existing CPR. Age categories will be fixed, and, in logistic regression, one dummy variable will be dropped from each categorical set to avoid the dummy variable trap.

All other variables (mRS, NIHSS, OTT) will be kept in their original format.

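### VKA exposure is declared a confounder and encoded but enters no stated analysis, so the anticoagulation decision curves rest on a part-treated risk

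*Protocol article*

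**What the plan says.** **Cohort.** Section 2.3 admits a patient with AF who "was treated with vitamin K antagonists (VKAs) or without any antithrombotic medication". The two groups are then analysed together. Section 2.7 counts them as one sample ("Given that our sample size is 2763 patients"), section 2.12.4 validates CHA2DS2-VASc on the whole AF dataset, and the 75/25 split under Model Building preserves the outcome distribution only.

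**VKA exposure.** Section 2.5 states: "The measured confounding variables are antithrombotic treatment (VKAs or none), start and end days of VKA administration, IVT, and OTT". The missing-data text in section 2.12.2 scales VKA days within fold, and Variable Encoding adds: "The number of days of VKA use over 90-day follow-up will be treated as a continuous variable".

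**Model inputs.** Section 2.4 says: "The predictor variables in the updating analyses are the constituent features of CHA_2_DS_2_-VASc", without the S2 item and with previous stroke added. CPR Development counts eight features: five comorbid items, sex and two age categories. VKA is not among them.

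**Decision.** CPR Evaluation says: "For early secondary prevention of AFAIS, oral anticoagulation is the treatment". It computes net benefit at thresholds 0.01–0.20 and calls a rule useful only where it beats both treat-all and treat-none.

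**Benchmark.** Section 2.11 records that CHA2DS2-VASc was developed in patients with "use of neither VKAs nor heparin at discharge".

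**The concern.** A decision curve for giving a treatment needs the risk a patient runs without that treatment. Here an unstated share of the cohort received an oral anticoagulant during the 90 days over which recurrence is counted, and the Introduction itself calls recurrence highly modifiable by oral anticoagulants. If VKA works as the protocol says, some patients who would have had a recurrence untreated are recorded as event-free. Where their predicted risk exceeds the threshold, they count as false positives.

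Three results are exposed:

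- **Absolute risk.** The pooled figure is lower than the risk of the untreated patient about whom the decision is made.
- **Calibration of CHA2DS2-VASc.** A score derived in patients on neither VKA nor heparin at discharge is tested in a partly treated cohort, so part of any miscalibration may reflect treatment rather than the score.
- **The useful-or-harmful verdict.** The treat-all line crosses treat-none at the observed prevalence, so a lower pooled prevalence moves the crossing point.

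Table 3 gives clinical utility precedence in interpretation, so the main conclusion is the one affected.

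**Working it through.** **1. Cohort figures.** 2763 × 0.75 = 2072.25 and 2763 × 0.25 = 690.75, matching the stated 2072 and 691. No stated figure is in dispute; the point concerns what the figures represent.

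**2. Where VKA exposure could enter.**

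| Place | Content | VKA used? |
|---|---|---|
| 2.4, CPR Development | eight model features | no |
| 2.12.4, Table 1 | validation on the entire AF dataset | no |
| 2.6 | Cox sensitivity analysis, death as censoring | no |
| Imputation Diagnostics | complete-case sensitivity analysis | no |
| Gender Bias, Age Bias | subgroups by sex and age | no |
| CPR Evaluation, Tables 3 and 4 | decision curves, test tradeoff | no |

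**3. Effect on absolute risk.** Let *f* be the share on VKA and RR the risk ratio on VKA versus none. Neither is in the documents, so both are assumed. If VKA use is unrelated to risk,

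pooled risk ÷ untreated risk = 1 − *f* + *f* × RR.

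| *f* | RR | Ratio |
|---|---|---|
| 0.3 | 0.60 | 0.70 + 0.180 = 0.88 |
| 0.3 | 0.35 | 0.70 + 0.105 = 0.805 |
| 0.5 | 0.60 | 0.50 + 0.300 = 0.80 |
| 0.5 | 0.35 | 0.50 + 0.175 = 0.675 |

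**4. Effect on the treat-all line.** By the protocol's formula, treat-all net benefit is *p* − (1 − *p*) × *p*t/(1 − *p*t). Assume an untreated risk of 12% and a threshold of 0.10, where the odds are 1/9.

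- Untreated: 0.12 − 0.88/9 = +0.022.
- Pooled, *f* = 0.5, RR = 0.5 (ratio 0.75): risk 9.0%, and 0.09 − 0.91/9 = −0.011. A simulation of this case gave 8.9% and −0.012.
- Pooled, *f* = 0.3, RR = 0.60: risk 10.56%, and 0.1056 − 0.8944/9 = +0.006.

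The crossing with treat-none moves from 12% to 9.0% in the second case and to 10.56% in the third. Between the old and new crossing points the better default strategy switches. Whether a given threshold falls in that interval depends on the assumptions.

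**5. Effect on the score association.** Simulation inputs, all assumed:

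- score: rounded normal (mean 5.2, SD 1.4), held to 2–9;
- untreated logit risk: −2.55 + 0.15 × (score − 5.2), giving risk 7.4%, OR per point 1.16 and AUC 0.56;
- *f* of 0.3 or 0.5, RR of 0.35 or 0.60;
- log-odds of VKA changing by −0.3, 0 or +0.3 per point.

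| VKA use as score rises | OR per point | AUC |
|---|---|---|
| falls | 1.19–1.24 | 0.569–0.585 |
| unrelated | 1.16 | 0.56 |
| rises | 1.07–1.13 | 0.528–0.546 |

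With no true effect and VKA use falling with score, the OR is 1.03–1.08. The direction of bias follows the assumed allocation, and every AUC stays below 0.6.

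**The case against.** **What stands.** Risk under care received is a legitimate prognostic target, and section 2.11 calls the broad filters deliberate, for applicability. The mismatch arises when absolute risk, calibration and net benefit are read as guiding a decision to anticoagulate; it does not invalidate every analysis. The article is condensed, and its supplementary files, which are not shown, could hold an adjustment. The bias would be small if few patients took VKA or its 90-day effect were weak. Section 2.11 also describes the development cohort by treatment at discharge only, which does not make it anticoagulant-free over follow-up.

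**Stronger readings the documents do not support.**

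- A reader might infer that VKA exposure is ignored altogether. It is declared, scaled and encoded. It is also absent from the variables that section 2.12.2 reserves for imputation only, which suggests an intended role. That role is never stated.
- A reader might take the Introduction's report that "patients with higher CHA_2_DS_2_-VASc scores were paradoxically less likely to receive antithrombotic therapy" as showing how VKA was allocated here. It comes from other studies and concerns antithrombotics in general, while this cohort is limited to VKA or nothing.
- A reader might expect the AUC verdicts in Table 1 to change. No AUC in the working crosses 0.6 or 0.7.
- A reader might expect the ranking of the rules to change. All rules share one test set, and no ranking was computed.
- Not every recurrence on VKA is a true positive; that holds only where predicted risk exceeds the threshold.

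**Conclusion.** The point holds in this form: a variable that the protocol calls a confounder and prepares for analysis has no stated analytic role, and decision curves about giving oral anticoagulation are drawn on a cohort partly given it. This is more than missing detail, because the article fixes the predictors, validation set, sensitivity analyses and decision curves, and followed as written these yield a part-treated risk.

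The size cannot be derived from the documents. Under VKA shares of 30–50%, risk ratios of 0.35–0.60 and allocation unrelated to risk, pooled risk is about 0.68–0.88 of untreated risk. In one illustration (untreated risk 12%, half on VKA, risk ratio 0.5) treat-all net benefit at threshold 0.10 changes sign, from +0.022 to about −0.011; with a smaller share and weaker effect it stays positive. Score weights may be biased in either direction, depending on how VKA use relates to the score.

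**What to change.** 1. In section 2.6 and CPR Evaluation, state the target risk: without anticoagulation, or under care received.
2. In section 2.12.4 and CPR Evaluation, add an untreated-risk calibration and decision curve for CHA2DS2-VASc and each updated rule. Censor follow-up at VKA start, with inverse-probability-of-censoring weights from baseline variables.
3. Base any conclusion about starting anticoagulation on that analysis, and label the pooled curve as risk under care received.
4. Do not enter total VKA days over follow-up as an ordinary covariate, and do not split naively by ever or never on VKA. Both are post-baseline and cut short by recurrence, haemorrhage or death. Any report by VKA status should use status at a fixed early landmark.

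**Cost.** VKA start and end days are already extracted (section 2.3), so this needs protocol wording and one added set of analyses. The price is precision: at 5% risk, the lower end of the protocol's range, the test set holds 691 × 0.05 ≈ 35 events before censoring removes any, so intervals will be wide. The weights also assume no unmeasured determinants of VKA start, which should be stated as a limitation.

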Primary: Does the acute context of AFAIS, and the importance of the index event, call for a CPR bespoke to early secondary prevention? In other words, are the main effects of the constituent features of CHA_2_DS_2_-VASc different post-stroke? Besides main effects, are there synergistic or other non-linear interaction effects between stroke history and the constituent features of CHA_2_DS_2_-VASc that can further improve prediction of 90-day AFAIS recurrence? Secondary: How do CPRs trained to capture 90-day AFAIS recurrence perform with regard to secondary outcomes (7-day recurrence, 7- and 90-day HT, 90-day decline in functional status, and 90-day all-cause mortality)? Exploratory: How do CPRs trained to capture 90-day AFAIS recurrence perform with regard to recurrence among non-AF AIS patients?	Primary: LR and XGBoost can capture the main effects of the constituent features of CHA_2_DS_2_-VASc in the context of secondary prevention. XGBoost is also equipped to capture complex functional relationships between the features. The outputs of these models can be employed to construct CPRs that outperform CHA_2_DS_2_-VASc for predicting 90-day recurrence in AFAIS patients. Specifically, fair (AUC < 0.8) to good (< 0.9) discrimination can be achieved for this high-risk group, alongside improved calibration and clinical utility relative to CHA_2_DS_2_-VASc. Secondary: The resulting CPRs also outperform CHA_2_DS_2_-VASc for predicting secondary outcomes.	LR and XGBoost models: Discrimination assessed using AUC and calibration curves. Calibration assessed using calibration curves, slopes, and Brier scores. Additional metrics: F1 score, accuracy, precision, sensitivity, specificity, Youden index, PPV, NPR, PLR, NLR. Resulting CPRs: Discrimination assessed using AUC and calibration curves. Calibration assessed using calibration curves, slopes, and Brier scores. Clinical utility assessed via DCA relative to default strategies as well as CHA_2_DS_2_-VASc. Test tradeoff analysis will be used to balance ease-of-use with clinical utility.	Primary: LR—680 patients deemed necessary, see Appendix S5.3 in Supplementary Materials file S3. XGBoost—learning curve analysis and KL divergence will afford post hoc insight on suitability of sample size. 75% of AF dataset will be used, comprising 2072 AFAIS patients. Remaining 25% (691 patients) will be withheld as test set. Secondary: Entire AF dataset will be used, comprising 2763 AFAIS patients. Exploratory: Entire non-AF dataset will be used as supplementary test set, comprising 7809 AIS patients.	Models will be instantiated (LR with L2 regularisation and XGBoost with default hyperparameters) on AF dataset, randomly split into training (***T***, 75%) and test sets (***t***, 25%), preserving distribution of outcomes. Nested cross-validation (5 × 2) will be employed for training and hyperparameter tuning. After hyperparameters are optimised, final models will be retrained using the entire training set. The test set ***t*** will then be used for evaluation of final LR and XGBoost models, focusing on discrimination and calibration. Feature importance will be reported via coefficients and odds ratios (ORs) for LR and feature gain for XGBoost. To derive CPRs from these models, SHAP will quantify both main effects and interaction effects of predictor variables. Main effects, represented by mean SHAP values, will be used to rank and assign scores to each predictor, enabling the creation of interpretable and clinically applicable CPRs. Interaction effects, captured through SHAP interaction values, will further refine our CPRs by identifying significant synergistic or redundant relationships between predictors. These interactions will be incorporated into so-called ‘augmented CPRs’ in the form of accompanying rules. Both non-augmented and augmented CPRs will be evaluated on the test set ***t*** in terms of discrimination, calibration, and clinical utility. Clinical utility will be measured using NB via DCA, plotting NB against risk thresholds within the 0.01–0.20 range. The CPRs will be compared on the basis of clinical utility to one another, CHA_2_DS_2_-VASc, and default strategies (‘treat all’ and ‘treat none’). Test tradeoff analysis will evaluate whether any incremental benefit in clinical utility observed with augmented CPRs justifies the added complexity of incorporating accompanying rules. Secondary: CPRs (and not models) will be evaluated on the entire AF dataset for each secondary outcome via discrimination, calibration, and clinical utility. Exploratory: CPRs (and not models) will be evaluated on the entire non-AF cohort to assess generalisability and compare their clinical utility when applied to an unseen yet closely related patient population.	Discrimination will be classified as follows [101]: AUC of 0.81–0.90 = good, 0.71–0.80 = fair, 0.61–0.70 = modest, and 0.51–0.60 = poor. Miscalibration is detrimental to medical decision making and poor calibration has been coined the Achilles heel for CPR applicability [102]. As such, we consider at least as important as discrimination and give precedence to clinical utility, which provides a more comprehensive evaluation by integrating both discrimination and calibration when interpreting the performance of our CPRs. CPRs will be considered clinically useful at a given risk threshold only if their NBs exceed those of both default strategies. Of those deemed useful, we will rank the CPRs (including CHA_2_DS_2_-VASc) based on NB across the 0.01–0.20 risk thresholds. Test tradeoff (∆*N**B*) will be interpreted only insofar as spotlighting those CPRs which would be more conveniently deployable without sacrificing significant clinical utility.

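### Clinical usefulness, harm and the ranking against CHA2DS2-VASc are decided on net-benefit point estimates from 691 test patients, with no interval and no named contrast

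*Protocol article*

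**What the plan says.** The section CPR Evaluation sets a rule for each threshold: "A CPR will be considered clinically useful at a given risk threshold only if its NB exceeds that of both default strategies". The mirror rule is that "if a CPR’s NB is lower than either default strategy, it will be deemed clinically harmful". NB is computed "across the 0.01–0.20 risk threshold range". The CPRs are then compared by "ranking them based on descending NB, and identifying the three CPRs with the highest clinical utility".

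The interpretation column of Table 3 repeats the rule and brings the existing score into the ranking: "Of those deemed useful, we will rank the CPRs (including CHA_2_DS_2_-VASc) based on NB across the 0.01–0.20 risk thresholds". The same cell gives clinical utility precedence over discrimination and calibration. The hypothesis being served is "The outputs of these models can be employed to construct CPRs that outperform CHA_2_DS_2_-VASc for predicting 90-day recurrence in AFAIS patients".

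Section 2.12.1 plans two CPRs for each of three models, so six new CPRs and CHA2DS2-VASc make seven rules. They are evaluated on the hold-out set: "the remaining 25% (*n* = 691 patients) will be reserved for testing".

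Uncertainty is specified for other measures. The AUC has 1000 bootstrap replicates (2.12.4 and Model Evaluation) and DeLong intervals (Model Evaluation). LR odds ratios have confidence intervals, and SAGE values have standard errors. NB has none.

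**The concern.** The measure given precedence is the one judged without sampling error. Apart from an exact tie, the two labelling rules leave no inconclusive result: a CPR is useful or harmful at each threshold according to which side of the defaults its observed NB falls. The labels are applied to six CPRs over a range of thresholds, and the highest observed values are singled out. Chance alone can then produce a useful label somewhere on a curve, or place a new CPR above CHA2DS2-VASc. At stake are the statements that an updated CPR is clinically useful and that it has higher utility than the existing score.

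**Working it through.** **1. The plan's figures.** 0.75 × 2763 = 2072.25 and 0.25 × 2763 = 690.75, which reproduce the 2072/691 split. Section 2.7 uses recurrence of 0.05–0.25, so the test set holds between 0.05 × 691 ≈ 35 and 0.25 × 691 ≈ 173 events. The minimum of 680 patients in section 2.7 concerns prevalence precision, prediction error, shrinkage and optimism. It does not address NB comparisons, and the article states no error rate for the NB rule.

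**2. What the rule requires.** Write w = pt/(1 − pt).
- Against treat none: TP/N − w·FP/N > 0 is the same as TP/(TP + FP) > pt.
- Against treat all: the difference is w·TN/N − FN/N, which is positive when FN/(FN + TN) < pt.

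So the flagged patients must run above pt and the unflagged below it. For a worthless score at a fixed pt near the true prevalence, these are two independent chances of about 1/2, giving about 1/4. If pt equals the prevalence observed in the test set, NB reduces to prevalence × (TPR − FPR) and the two conditions coincide, giving about 1/2. That threshold is known only after the data are seen.

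**3. Simulation with worthless scores.** From the plan: 2072/691 patients, eight features, 1–2–3 point scores, Platt or isotonic calibration (section 2.8), and the article's NB formula. Assumed: feature prevalences, the correlation among the six CPRs, calibration of the point scores in the training set, and steps of 0.01 (20 thresholds). There were 1000 runs per cell. The ranking rows use mean NB over the range, without first restricting to CPRs deemed useful.

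| Event | Recurrence 0.05–0.20 | Recurrence 0.25 |
|---|---|---|
| One CPR useful at one threshold (highest over thresholds) | 0.20–0.26 | 0.02–0.14 |
| One CPR useful at 1 or more of 20 | 0.43–0.64 | 0.03–0.16 |
| At least one of six useful at 1 or more of 20 | 0.61–0.82 | 0.03–0.18 |
| One CPR useful at more than half of the thresholds | 0.00–0.04 | 0.00–0.01 |
| One CPR above worthless CHA2DS2-VASc | 0.36–0.49 | 0.03–0.17 |
| Best of six above worthless CHA2DS2-VASc | 0.59–0.66 | 0.04–0.21 |

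Two further sets of runs used LR-based proxies for all three models and Platt-type calibration.
- The first gave 62–80% (any of six useful somewhere), 43–52% (one CPR) and 67–72% (best of six ranked above) at recurrence 5–20%, falling to about 4–7% at 25%.
- The second, at recurrence 0.05, 0.10 and 0.20 with its own assumed prevalences, gave 76–90%, 56–72% and 61–67%.

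**4. Effect of an interval.** Suppose the lower 95% limit of the paired NB difference must exceed 0 against both defaults at each threshold. For one worthless CPR at recurrence 0.05–0.20, the chance of a useful label at one or more thresholds changes as follows:
- Platt: from 0.43–0.58 to 0.03–0.06.
- Isotonic: from 0.46–0.63 to 0.06–0.25. The 0.25 arises at recurrence 0.05, where few events make the normal-approximation interval too narrow.

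For an assumed informative Platt-calibrated CPR, the same chance falls from 1.00 to 0.74, 0.93 and 0.96 at recurrence 0.05, 0.10 and 0.20. With a Bonferroni correction over 20 thresholds it is 0.39, 0.56 and 0.69.

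**5. The AUC part of the hypothesis.** With 35 events and 656 non-events, the null standard error of the AUC is √(692/(12 × 35 × 656)) ≈ 0.050. A worthless score would need (0.71 − 0.50)/0.050 ≈ 4.2 standard errors to reach the band Table 3 calls fair.

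**The case against.** Several counter-arguments have force.

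- **The rule works per threshold.** A reader might infer that it labels any given worthless CPR useful most of the time. The documents do not support that: with the calibration planned in section 2.8, the chance at a fixed threshold is at most about 1 in 4. The larger figures need any of six CPRs at any threshold, an event the plan does not itself define as success.
- **The recurrence rate matters.** The plan's range runs to 0.25, and there the problem nearly vanishes because the prevalence lies above the threshold range.
- **Table 3 asks for more than NB.** A reader might infer that the whole claim of superiority would be reached in most studies with no real gain. It would not: the hypothesis also expects fair to good AUC and better calibration, and step 5 shows that a worthless score would almost never reach the fair band.
- **There are safeguards.** NB is computed on held-out data. Small NB differences are read as favouring the simpler CPR. The LR and XGBoost CPRs are checked in 7809 non-AF patients, and a separate external validation is promised.
- **Intervals around decision curves may be detail left to a fuller document,** and choosing by expected NB is a defensible decision-theoretic position.

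The first three limit the size of the point and are accepted. The safeguards do not remove it. A hold-out set removes training optimism but not sampling noise or best-of-six selection. The non-AF check omits the MLP CPRs and states no interval either, and external validation lies in the future. Nor is this only missing detail, because the article fixes the decision rule. Its wording is formally a necessary condition, but no second condition is given, and both the harm rule and the ranking of CPRs deemed useful treat it as decisive.

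**Conclusion.** The point holds for the utility and ranking claims. At recurrence of 5–20%, at least one of six worthless CPRs is labelled useful somewhere in 0.01–0.20 in roughly 60–80% of test sets, and one set of assumed inputs reached 90%. The best of six outranks an equally worthless CHA2DS2-VASc in about 60–70%. These figures rest on assumed feature prevalences, simplified models, 0.01 steps and calibrated scores.

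When the CHA2DS2-VASc weights were made exactly right, at least one new CPR still outranked it in 50–58% of runs. Where AUCs were recorded, that was a near-tie (about 0.594 against 0.602). A reader might extend this to cases where CHA2DS2-VASc is clearly better, but those were not examined.

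**What to change.** In CPR Evaluation and the interpretation column of Table 3, before the test set is opened:

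1. Name one primary contrast: one CPR, chosen by nested cross-validation in the training set, against CHA2DS2-VASc recalibrated to 90-day risk in the training set. Compare them on NB at one or a few named thresholds, or averaged over 0.01–0.20.
2. Extend the planned 1000-replicate bootstrap to paired 95% intervals for NB(CPR) − NB(better default) and NB(CPR) − NB(CHA2DS2-VASc).
3. Base any statement that the CPR is useful, harmful or outperforms on that contrast and its interval, and call the result inconclusive when the interval includes 0.
4. Keep the per-threshold curves and the seven-way ranking as descriptive results, shown with intervals.

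A blanket correction over every threshold is not proposed; step 4 of the check shows how many informative CPRs it would lose. The cost is plan wording and one extra bootstrap run. The downside is that fewer CPRs, including some that are truly useful, will be firmly declared useful or better.
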